#### Additional analyses

We plan to conduct subgroup analyses with strong biological rationale and possible interaction effect. The subgroup analysis will compare odds ratios for the use of titanium clips during lymphadenectomy versus lymphadenectomy without the use of clips.

A sensitivity analysis of the primary endpoint will adjust for the pre-randomization variables which might reasonably be expected to be predictive of outcomes.

#### Missing data

Since the intervention is an operative procedure at the beginning of the study period non-adherence is no matter of discussion in our cohort. Once a patient is enrolled or randomized, the study site will make every reasonable effort to follow the patient for the entire study period. If a patient is not willing to send back the information of the follow-up after 6 months, we will report reasons for withdrawal for each randomization group and compare the reasons qualitatively.

### Data monitoring

#### Formal committee

No data monitoring committee will be installed. However, in order to ensure patient safety, all perioperative complications will be assessed and analyzed.

#### Safety and harms

We do not expect any unexpected or unexplained harms or adverse events. In our study, adverse events will be defined as any unfavorable medical occurrence in a subject without regard to the possibility of a causal relationship. Adverse events will be collected from day of operation until the day of discharge from our department and at the 6-month follow-up after the subject has provided written informed consent an enrolled in the study.

Most adverse events that are seen in patients after RARP are anticipated (symptomatic lymphocele, deep vein thrombosis, drainage insertion, urinary tract infection, hematuria, lymphedema, and erysipelas). However, all adverse events will be recorded. Serious adverse events (SAE) between study enrollment and hospital discharge will be reported. A SAE for this study is any untoward medical occurrence that is believed by the investigators to be causally related to the intervention and results in any of the following: life-threatening condition (immediate risk of death), severe or permanent disability, or prolonged hospitalization. Investigators will determine relatedness of an event to intervention as well as whether the event is unexpected or unexplained given the subjects’ clinical course and previous medical conditions.

The investigators inform the principal investigator (PI) about harms. Depending on harms, the PI might inform the local ethics committee and terminate the study.

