**Methods/design:**

PELYCAN is a parallel-group, patient- and assessor-blinded, phase III, adaptive randomized controlled superiority trial. Men with histologically confirmed prostate cancer who undergo transperitoneal RARP with pelvic LND will be randomly assigned in a 1:1 ratio to two groups—either with creating a peritoneal flap (PELYCAN) or without creating a peritoneal flap (control). Sample size calculation yielded a sample size of 300 with a planned interim analysis after 120 patients, which will be performed by an independent statistician. This provides a possibility for early stopping or sample size recalculation.

Patients will be stratified for contributing factors for the development of postoperative lymphoceles. The primary outcome measure will be the rate of symptomatic lymphoceles in both groups within 6 months postoperatively. Patients and assessors will be blinded for the intervention until the end of the follow-up period of 6 months. The surgeon will be informed about the randomization result after performance of vesicourethral anastomosis. Secondary outcome measures include asymptomatic lymphoceles at the time of discharge and within 6 months of follow-up, postoperative complications, mortality, re-admission rate, and quality of life assessed by the EORTC QLQ-C30 questionnaire.

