## Introduction and background

Pelvic lymphoceles present a common complication after RARP with lymph node dissection (LND) in approximately 10–18% of the cases [1–3]. Most lymphoceles are asymptomatic; nevertheless, in 1 to 15% of lymphoceles, symptoms occur. Obstruction of blood flow in the iliac vessels may cause thrombosis subsequently leading to venous thromboembolism. Hence, lymphoceles should be treated if they are symptomatic or impair venous blood flow. The current standard is percutaneous drain placement (ultrasound or computed tomography guided). However, in some cases, high flow rates of lymphatic fluid last for weeks thus causing substantial morbidity for the patient with additional hospital admission and loss in quality of life [1, 4–6]. In these cases, peritoneal fenestration is recommended [7].

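### The SAE rules tie seriousness to believed flap causality, omit death and new admission, and stop at discharge, so SAE counts are not comparable between arms and miss later serious events

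*Protocol article*

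**What the plan says.** All the SAE rules stand in the protocol article under Safety and harms.

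- **Causality:** "A SAE for this study is any untoward medical occurrence that is believed by the investigators to be causally related to the intervention".
- **Criteria:** the event must also result in one of "life-threatening condition (immediate risk of death), severe or permanent disability, or prolonged hospitalization".
- **Window:** "Serious adverse events (SAE) between study enrollment and hospital discharge will be reported".

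The same section treats ordinary adverse events (AEs) differently.

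- **Causality:** "adverse events will be defined as any unfavorable medical occurrence in a subject without regard to the possibility of a causal relationship".
- **Window:** "Adverse events will be collected from day of operation until the day of discharge from our department and at the 6-month follow-up".
- **Completeness:** "However, all adverse events will be recorded".

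Other sections bear on the point.

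- The abstract (Methods/design) names "postoperative complications, mortality, re-admission rate" among the secondary outcomes.
- Secondary outcome measures lists rehospitalisation within 6 months, re-intervention, deep vein thrombosis, lymphedema or erysipelas, and complications graded by Clavien-Dindo and the Comprehensive Complication Index. The graded complications stand under the perioperative parameters. Mortality is not in this list, and Table 1 has no row for it.
- Blinding and blinding mechanism keeps patients, outcome assessors, post-discharge care providers and data collectors unaware of the arm.
- Formal committee says that no data monitoring committee will be set up, and that perioperative complications will be assessed and analysed.

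**The concern.** An SAE listing is normally read by arm, and a reader will do so here whether or not a test is planned. That reading is fair only if the same kind of event can count in both arms. Here, seriousness depends on a belief that the intervention caused the event, and only one arm receives the intervention. The filter also lets prior belief about the flap decide what is counted, and the Discussion already says that, as far as the authors know, the procedure is harmless.

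The window is the second problem. The primary endpoint runs to 6 months, and the Discussion presents coverage beyond 90 days as an advantage over other trials. The Introduction describes prolonged lymphatic drainage as "causing substantial morbidity for the patient with additional hospital admission". That sentence concerns lymphoceles, not harm from the flap, but it shows that the authors regard readmission as a serious consequence in this population. Under the stated rules a readmission falls outside the SAE criteria and outside the window.

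At stake is how serious harm is reported for a technique that the abstract says may be suggested as a new standard if superior. The trial has no data monitoring committee and no auditing, and it may grow to 1000 patients.

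**Working it through.** No figure in the plan is disputed, so the check is mainly one of text against text.

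**1. Can a control event be an SAE?** Intervention description assigns the intervention to group A, and the Discussion says that the study has one intervention, the flap. An untoward event in a patient without a flap cannot be caused by a flap. Applied correctly, the definition therefore excludes control events, while the same events in group A may count if judged related. The two counts measure different things.

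**2. Who can apply the definition?** Judging relatedness to the flap requires knowing whether one was made. The operating surgeon learns the arm after the anastomosis, and the surgical assistant knows it the evening before. Assessors and later care providers are blinded until 6 months. Either the investigator assessing relatedness knows the arm, or that investigator cannot apply the definition properly. The article does not say which.

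**3. Which events are left out?**

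| Serious event | AE record | SAE as written |
|---|---|---|
| Any arm, judged unrelated to the flap | Yes | No |
| Death before discharge, judged related | Yes | Only if another listed criterion also applies |
| New admission after discharge | Yes, at 6 months; also a secondary endpoint | No |
| Any serious event between discharge and 6 months | Yes, at 6 months | No |

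**4. How well do the other data fill the gap?** Rehospitalisation, re-intervention, thrombosis and lymphedema or erysipelas are collected in both arms. Three weaknesses remain. Complication grading is listed as perioperative. The 6-month questionnaires allow only yes or no answers. Table 1 has no row for general adverse events or for mortality.

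**5. Scale.** The inputs come from Sample size: 10% versus 2%, 80% power, one-sided 0.025, 141 per arm, 282 in total, about 6% drop-out, 300 patients.

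The plan's own figure first, by the pooled-variance formula without continuity correction:

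n = [1.96·√(2·0.06·0.94) + 0.8416·√(0.10·0.90 + 0.02·0.98)]² / 0.08² = (0.658 + 0.279)² / 0.0064 ≈ 137.2, so 138 per arm. The stated 141 is within 3% of this. Drop-out: 282 / 0.94 = 300, or 150 per arm.

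Power for a difference in serious events at 150 per arm, two-sided 0.05, is Φ[(|p₁ − p₂| − 1.96·SE₀) / SE₁], with SE₀ pooled and SE₁ unpooled. The rates below are assumptions; the document gives none.

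| Assumed rates | SE₀ | SE₁ | Power |
|---|---|---|---|
| 1% vs 3% | 0.01617 | 0.01612 | 23% |
| 2% vs 5% | 0.02122 | 0.02115 | 29% |
| 1% vs 5% | 0.01970 | 0.01956 | 53% |

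If no serious event occurred among 150 flap patients, the one-sided 95% upper bound would be 1 − 0.05^(1/150) ≈ 2.0%.

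**The case against.** The strongest reply is that the SAE label matters little here. Adverse events are defined without a causality condition, all are recorded, and collection continues at 6 months. Readmission, re-intervention and thrombosis are secondary endpoints in both arms. No SAE endpoint or SAE test is planned; the article says only that SAEs will be reported. What the principal investigator acts on is harms in general, not SAEs alone. Most of this stands, and it limits the point.

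A reader might infer that the trial cannot show whether the flap causes serious harm. The document does not support that, because all-cause data exist in both randomised arms. A reader might also infer that the control-arm SAE count must be exactly zero. That does not follow either. The rule turns on what investigators believe, a blinded investigator could attribute a control event to the intervention, and Table 1 places both groups under its intervention heading. Nor can the SAE be called the main safety trigger, given the broader wording about harms.

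The reply does not rescue the definition itself. An SAE report produced under these rules would still differ in meaning between arms and would stop months before follow-up ends. The AE and secondary-outcome data do not clearly grade severity after discharge. Nor does the reply resolve where mortality is recorded.

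**Conclusion.** The point holds in a limited form and should be fixed. As written, SAE counts are not comparable between arms. Serious events after discharge are never SAEs, and deaths are SAEs only through another criterion. Evidence on serious harm then rests on the all-cause AE data and the secondary outcomes. Those data are usable, so the defect weakens the safety reporting without disabling it. The primary endpoint, its estimate and its test are untouched.

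This rests on reading the intervention as the flap alone, as the Discussion does. If it meant the whole operation, control events could qualify, but the omitted criteria and the early cut-off would remain. The share of serious events lost cannot be computed, because the document gives no serious-event rates. Under the assumed rates above, power at 150 per arm is about 23% to 53%. Repairing the definition makes the report complete and fair; at the planned size it does not make the trial able to settle rare harm.

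**What to change.** Amend Safety and harms as follows.

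- Define an SAE as any untoward event in either arm, regardless of causality, that results in death, is life-threatening, leads to initial or prolonged hospitalisation, or causes severe or permanent disability.
- Collect SAEs from surgery to the 6-month follow-up.
- Record relatedness as a separate field, judged where possible by someone unaware of the arm.
- Tabulate SAEs by randomised arm.
- Reconcile mortality between the abstract, the secondary endpoint list and Table 1.

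The cost is more SAE forms, plus retrieval of outside records for events treated elsewhere, since yes or no questionnaire answers will not establish seriousness. No visit is added, because patients and their outpatient urologists are already contacted at 6 months. Protocol amendments gives the route. At submission 140 of 300 patients had been randomised; for them the new definition can be applied to the adverse events already recorded and to the 6-month contact.

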#### Auditing

There will not be any auditing. Since there is no sponsor and the investigators do not have a financial nor a non-financial incentive neither, the study will be performed independently.

## Ethics and dissemination

### Research ethics approval

Ethical approval has been obtained from the University of Heidelberg’s Ethics Committee II (Medical Faculty Mannheim 2019-1127 N (Additional file 3)) with respect to scientific content and compliance with applicable research and human subjects’ regulations. The study protocol, participant education, and the informed consent form have also been reviewed by that ethical committee. Written, informed consent to participate will be obtained from all participants.

### Protocol amendments

If any modifications to the protocol will be necessary, which may have an impact on the conduct or the potential benefit of the study or affect the patient safety, a formal amendment to the protocol will be required. These modifications include changes of the study objectives, study design, patient population, study procedures, or significant administrative aspects.

The amendment will be agreed upon by the PI and it has to be approved by the ethics committee prior to implementation. Any of these modifications will be described in the trial report to prevent bias and provide trial integrity.

### Ancillary studies

Every participant provides written consent for ancillary studies. This is included in the informed consent material. Therefore, and due to the fact that no biological specimens will be taken, no additional consent is needed.

### Confidentiality

All study-related information will be stored securely at the study site. All participant information will be collected in strictly pseudonymous form and be stored in a password-protected file. The follow-up document, if not obtained electronically, will be stored in a locked file cabinet in areas with limited access. All reports, data collection, process, and administrative forms will be identified by a coded ID only to maintain participant confidentiality. The data and the linking code will be stored in separate locations using encrypted digital files within password-protected folders and storage media. All records that contain names or other personal identifiers will be stored separately from study records. All local databases will be password-protected. Participants’ study information will not be released outside of the study without the written permission of the participant. The access to the data is limited to the minimum number of individuals necessary for quality control and analysis. There will not be any data transmission.

### Access to data

The principal investigator will be given access to the full data sets. To ensure confidentiality, data dispersed to all other investigators and project team members will be blinded of any identifying participant information.

### Ancillary and post-trial care

Due to the operative-interventional character of the study access to the intervention (peritoneal flap) cannot be provided to the control group. Since we do not expect any complications, we do not consider post-trial or ancillary care necessary.

### Dissemination policy

#### Trial results

The results of the PELYCAN trial will be submitted to a peer-reviewed journal regardless of the study outcome. Every attempt will be made to reduce to an absolute minimum the interval between the completion of data collection and the release of the study results. We expect to take about 3–6 months to compile the final results paper for an appropriate journal.

#### Authorship

Authorship will be based on the ICMJE (International Committee of Medical Journal Editors) recommendations. Participants who do not fulfill the authorship criteria will be listed as “collaborator.”

### Trial status

The first patient was randomized on September 2, 2019. At the time of the protocol submission (August 16th, 2020), our center was actively recruiting patients for the trial and 140 of 300 patients had been randomized. Inclusion is according to schedule. This protocol version is 1.0 (October 17th, 2020).

## Discussion

RARP is a surgical gold standard for localized PC patients. In most cases, it is performed in combination with LND. Symptomatic lymphoceles are a common complication after LND. Different approaches have been described to reduce lymphocele-development after RARP [12–15]. A recently published systematic review could not find evidence among these methods [41]. However, they stated that peritoneal reconfiguration could present a reasonable option and called for further data [41]. This has been suggested in several studies [6, 16–19]. The only RCT, which has been published recently, showed no difference in symptomatic lymphoceles regarding the creation of a PF [20]. However, that study was limited due to a low sample size [20].

In a thorough research including the German Clinical Trials Register and ClinicalTrials.gov, we could identify only two ongoing RCTs assessing peritoneal flaps in order to prevent or decrease lymphoceles after RARP with LND. One of these is a multicenter study (DRKS00015720), whereas the other is designed single center (NCT03567525). Both the studies’ primary endpoint is the prevalence of lymphoceles within 90 days postoperatively. While their primary endpoint includes both asymptomatic and asymptomatic lymphoceles, the primary endpoint of the PELYCAN study is symptomatic lymphoceles. Furthermore, lymphoceles which form > 90 days postoperatively will not be covered by these studies. Additionally, none of the mentioned RCTs has published study protocols.

The investigator-initiated PELYCAN study is an RCT to compare RARP and LND with creation of PF versus RARP and LND. It focuses on the difference of postoperative lymphoceles. The primary endpoint is symptomatic lymphoceles within 6 months. This endpoint is one strength of the PELYCAN study as it is highly objective and standardized.

The PELYCAN study consists of one intervention, which is the creation of a PF. The PF is only created in the intervention group and performed by bilateral incision of the peritoneum with subsequent fixation at the pelvic floor. For fixation 2 interrupted 4/0 Vicryl sutures are used. This is an easy, suitable and expeditious procedure. To our knowledge, this procedure does not produce any harms.

Blinding of patients in surgical trials usually is difficult. Given the fact that the intervention does not include the surgical access, patient blinding will be possible without limitations.

One point of discussion is that due to the nature of the intervention, a complete double-blinding in terms of blinding the surgeon is impossible. However, until the vesicourethral anastomosis is finished, the surgeon will remain blinded. This late point of unblinding guarantees a consistent procedure and thereby lowers the surgeons’ bias. Additionally, outcomes assessors will be blinded until 6 months postoperatively.

In conclusion, the PELYCAN study is a parallel-group, patient- and assessor-blinded, phase III, adaptive randomized controlled superiority trial investigating the impact of PFs on symptomatic lymphoceles following RARP with LND performed by experienced surgeons beyond the learning curve. The PELYCAN study has the potential to initiate a paradigm shift in order to avoid postoperative lymphoceles and further refine the technique of RARP.

## Data Availability

The principal investigator and [name] will be given access to the full data sets. To ensure confidentiality, data dispersed to all other investigators and project team members will be blinded of any identifying participant information.

## Abbreviations

AT: As treated
BMI: Body mass index
CONSORT: Consolidated Standards Of Reporting Trials
EORTC: European Organisation for Research and Treatment of Cancer
ITT: Intention to treat
LND: Lymph node dissection
PF: Peritoneal flap
PI: Principal investigator
PP: Per protocol
QoL: Quality of life
RARP: Robotic-assisted radical prostatectomy
RCT: Randomized, controlled trial
SAE: Serious adverse event
SPIRIT: Standard Protocol Items: Recommendations for Interventional Trials
